## Methods and analysis

### Trial design

This protocol describes the methodology of a parallel-group, two-arm randomized controlled trial, which will employ an intervention condition (CALMA app) and a control condition (Treatment as usual-TAU) with a 3-month follow-up for each participant. Participants will be assessed at four timepoints: day-0 (baseline), day-30, day-60, and day-90.

The intervention group will receive the CALMA app and continue with the usual treatment in a public hospital mental health service. The CALMA app will be downloaded with the assistance of a team member into the participant’s smartphone during the first interview. In each follow-up interview (30-days and 60-days), the use of the app will be reinforced. The control group (TAU) will not receive the app but will keep doing the usual treatment provided in public hospitals throughout the study. The usual treatment in public hospitals in Argentina consists of a weekly visit to a psychologist and a monthly visit to a psychiatrist (in case the patient receives any pharmacological treatment). In the public hospitals of Argentina, there are no DBT programs, and most of the interventions are psychoanalytic.

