### Outcomes measures

#### Primary outcome measure

Suicidal behavior will be assessed using the Spanish version of the Self-Injurious Thoughts and Behaviors Interview (SITBI) (68, 69). This is a structured interview consisting of 169 items divided into 5 modules that examine the presence, frequency and characteristics of 5 types of self-injurious behavior: (a) suicidal ideation; (b) suicide plans; (c) suicidal gestures; (d) suicide attempts and (e) self-harm. The SITBI conceptualizes suicide risk on a continuum, starting with suicidal ideation (“thoughts of killing yourself?”), possibly accompanied by a suicide plan [“think about how you might kill yourself (e.g., taking pills, shooting yourself) or work out a plan of how to kill yourself?”] and in some cases by suicide attempt [“made a suicide attempt (i.e., purposefully hurt yourself with at least some intent to die)?”]. The construction of the questions in the original SITBI is consistent with the commonly accepted definitions of each type of behavior. The administration of the scale takes between 3 and 15 min.

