### Sample size

The sample size was calculated using the G*Power 3.1.9.4 statistical software according to the main objective. Considering a confidence level of 95%, a power of 80% and an effect size *d* = 0.85, 25 individuals per group are needed to detect a significant difference in the median frequency of self-injurious behaviors with the two tailed Mann–Whitney U test. Assuming a proportion of lost in the follow-up of 15%, then the study would have to start with 29 individuals per group.

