### Statistical analysis

To describe the sociodemographic characteristics of the patients in the two groups, absolute and relative frequencies (%) will be used for the qualitative variables, and the mean and standard deviation will be used for the only quantitative variable (age) if it presents a normal distribution according to the Shapiro–Wilk test. In case of presenting a non-normal distribution, the median and the interquartile range will be computed.

To compare the sociodemographic characteristics between the groups, the chi-square or Fisher’s exact test will be used for the qualitative variables, and the student’s t-test or the Mann–Whitney U test will be computed for the quantitative variable.

For all patients and at each follow-up moments, the difference between the frequency of each suicidal behavior and the baseline frequency will be calculated. Then it will be evaluated if these differences follow a normal distribution (Shapiro–Wilk test). In this case, the mean differences for each behavior between both groups will be compared using the t-Student test. Otherwise, the medians will be compared with the Mann–Whitney U test. The *p*-values obtained will be corrected according to the Bonferroni criterion.

To assess whether the change in emotional regulation mediates the change in the frequencies of each suicidal behavior, the difference between the value of the DERS scale at the last follow-up and the baseline will be calculated, and the Sobel test will be used on a regression model whose dependent variable will be the difference in the frequency of each behavior and the independent variable will be the treatment. Previously, the probability distribution of the quantitative variables will be evaluated and it will be considered whether it is necessary to carry out any transformation of data to guarantee compliance with the assumptions of the regression model.

Both for the frequencies of the different suicidal behaviors and for the DERS scale, the missing values will be imputed according with the multiple imputation method using chained equations (MICE) with appropriate models for each variable to be imputed, considering sociodemographic characteristics, the hospital of recruitment and the baseline measurements of frequencies and DERS scale as independent variables.

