Regarding acceptability, the UEQ Data Analysis Tool offers a benchmark to classify the application in 5 categories of 6 scales: excellent, good, above average, below average and bad allowing conclusions to be drawn about the relative quality of CALMA compared to other products.^2^

To evaluate and compare the time to readmission in patients enrolled during hospitalization, a Cox regression model will be adjusted, considering the treatment of each patient as the independent variable. For this, the time elapsed from study entry to readmission (event) or to loss of follow-up or final of the study (censoring) will be calculated. In all cases, a value of *p* less than 0.05 will be considered significant. Statistical analysis will be performed with RStudio 1.4.1106.

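### Single-step Bonferroni is valid here, but Holm's step-down procedure on the same tests gives the same 5% family-wise guarantee and can only add rejections: a cheap, low-severity improvement

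*Protocol article*

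**What the plan says.** - **Tests.** Statistical analysis: "For all patients and at each follow-up moments, the difference between the frequency of each suicidal behavior and the baseline frequency will be calculated". Each difference is then compared between arms by t-test or, if non-normal, by Mann-Whitney.
- **Correction.** The same section says the p-"values obtained will be corrected according to the Bonferroni criterion". It does not say whether the correction runs over behaviours, visits or both.
- **Level.** A p-value "less than 0.05 will be considered significant".
- **Visits.** Trial design: "Participants will be assessed at four timepoints: day-0 (baseline), day-30, day-60, and day-90", so there are three follow-ups.
- **Behaviours.** Primary outcome measure lists five SITBI types: "a) suicidal ideation; (b) suicide plans; (c) suicidal gestures; (d) suicide attempts and (e) self-harm". Three of them are behaviours if ideation and plans are set aside.
- **Size.** Sample size asks for 25 evaluable per group with 95% confidence, 80% power and "an effect size *d* = 0.85", and 29 per group after 15% loss.

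**The concern.** Bonferroni compares every p-value with 0.05/m, where m is the number of tests. Holm uses that threshold only for the smallest p-value and relaxes it after each rejection. Both guarantee family-wise error of at most 5% under any dependence, so Holm needs no further assumption, and nothing rejected by Bonferroni is lost. The usual reason to keep Bonferroni is that it gives simple simultaneous confidence intervals, and the article specifies none.

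At stake is how many effects can be claimed once one is established. With 29 patients per arm and several outcomes, a response across more than one behaviour or visit may be reported as isolated because the later p-values still face the strictest threshold.

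**Working it through.** **1. The plan's own figure.** Two-sided Mann-Whitney, alpha 0.05, d = 0.85, using noncentral-t power with n multiplied by the asymptotic relative efficiency (ARE):
- ARE 3/π (normal parent): 24 per group, power 0.820 at 25.
- ARE 0.864 (minimum): 27 per group, power 0.779 at 25.

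The stated 25 lies between these and is taken as reproduced. The 29 is also close (25/0.85 = 29.4; 25 × 1.15 = 28.75). This calculation is for one unadjusted test.

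**2. Possible families.** The article does not define the family, so these sizes are assumptions:
- one behaviour × 3 visits = 3 tests
- three behaviours × 3 visits = 9 tests
- five SITBI types × 3 visits = 15 tests

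**3. Thresholds.** Bonferroni rejects when p ≤ 0.05/m: 0.05/3 = 0.0167, 0.05/9 = 0.0056, 0.05/15 = 0.0033. Holm orders the p-values and compares the j-th smallest with 0.05/(m − j + 1), stopping at the first failure. For m = 9 the sequence starts 0.05/9 = 0.0056, 0.05/8 = 0.00625, 0.05/7 = 0.0071 and ends at 0.05. The first step is identical, so the two methods have the same chance of rejecting anything at all.

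**4. Average power per true effect at d = 0.85.** Simulated trials with 25 per arm, Mann-Whitney on change scores, and assumed correlations of 0.5 between visits and 0.4 between behaviours (4,000 trials per row):

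| Tests | Real effects | Bonferroni | Holm | Gain (points) |
|---|---|---|---|---|
| 3 | all | 67% | 75% | 8 |
| 9 | all | 49% | 62% | 13 |
| 9 | two of three behaviours | 51% | 57% | 6 |
| 9 | one of three behaviours | 49% | 51% | 2 |
| 15 | all | 43% | 55% | 12 |
| 15 | two of five behaviours | 41% | 44% | 3 |

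A separate simulation on the test statistics (normal approximation, equal correlation 0.5, 20,000 replicates) agrees in pattern. With 15 tests the gain is 0 points with one real effect (0.505 under both), 1 with three (0.503 to 0.513), 2 with five (0.502 to 0.522) and 11 with all fifteen (0.499 to 0.613).

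**5. Smaller effects.** At d = 0.324, the size of the pooled dialectical behaviour therapy effect on self-directed violence cited in the Introduction, with every effect real (normal approximation):
- 3 tests: 10.2% against 11.8%
- 9 tests: 4.9% against 5.8%
- 15 tests: 3.4% against 4.0%

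**6. Chance of at least one true finding.** With 15 tests and correlation 0.5 it is the same under both methods: 0.505 with one real effect, 0.756 with three and 0.937 with fifteen.

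**7. Realised family-wise error.**
- No real effects, 15 tests, correlation 0.5: 0.036 under both.
- 3 tests, two real, correlation 0.5: 0.018 Bonferroni, 0.039 Holm.
- 9 tests, two of three behaviours responding, correlations as in step 4: 1.2% Bonferroni, 2.5% Holm.

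All of these are below 5%.

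**The case against.** The strongest reply is that nothing in the article is wrong. Bonferroni is prespecified, controls family-wise error under any dependence, and is nowhere claimed to be the most powerful method. That stands: this is an efficiency choice, not an error.

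A reader might go further and infer that Bonferroni gives up power for no benefit in error control. That is too strong. The guaranteed level is the same, but when some nulls are true Bonferroni's realised error is lower (step 7). It also bounds the expected number of false rejections at alpha, which Holm does not, and it yields simple simultaneous intervals. The article specifies no intervals, but it is a condensed account and an analysis plan not shown here may do so.

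A reader might also take the 8 to 13 point gain as typical. It needs a d of 0.85 for every behaviour at every visit. The Introduction cites pooled effects of d = −0.324 and SMD −0.28 for the parent therapy, with no significant pooled effect on ideation. The Discussion reports a greater between-group decrease in the pilot only for ideation and suicidal gesture. The pilot's within-group decreases across several outcomes, reported in the Rationale, make a broad response conceivable but are only suggestive.

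Finally, the family is inferred. The wording supports behaviours by visits, but no count is given. Holm's advantage holds for any family of two or more tests; its size depends on which one is meant.

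**Conclusion.** The point holds as a low-severity improvement. For whatever family is kept, Holm gives the same 5% family-wise guarantee and never rejects less. The benefit is confined to further behaviours or visits after a first rejection: about 8 to 13 points of average power per true effect if all effects are real at d = 0.85, about 2 to 6 points if only some behaviours respond (nil if a single one of 15 tests has a real effect), and under 2 points if effects are near 0.32. These figures rest on 25 evaluable per arm, assumed correlations and assumed family sizes of 3, 9 or 15.

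A reader might infer that Holm would restore the planned power. It would not, because its first threshold is Bonferroni's. The Sample size section rests on one test at unadjusted 0.05. At 25 per group (ARE 3/π), power for a single test falls from 0.82 to 0.67, 0.52 or 0.45 at the Bonferroni threshold for 3, 9 or 15 tests. That is a separate matter which this change leaves open.

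**What to change.** In Statistical analysis, replace the reference to the Bonferroni criterion with: *Holm step-down procedure, two-sided family-wise 0.05*. In the same sentence, state the family: which SITBI behaviours and which of the day-30, day-60 and day-90 comparisons it contains. Either method needs that count. Make the change before unblinded data are analysed.

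The cost is one line of text and one argument to `p.adjust` in R, with no extra patients, visits or data. The downsides are the slightly higher realised family-wise error when some nulls are true, still at or below 5%, and less simple simultaneous confidence intervals. If the full analysis plan relies on such intervals, keeping Bonferroni is a reasonable choice and the reason should be stated.

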**Methods:**

To test the effectiveness, safety and level of engagement of the CALMA app in people aged 10 to 19 who are treated in mental health services of two public hospitals, we will conduct a parallel-group, two-arm randomized controlled trial. Participants will be assessed face-to-face and *via* video call at four timepoints: day-0 (baseline), day-30, day-60, and day-90. A total of 29 participants per group will be included. Change in the frequency of suicidal and non-suicidal self-injurious behaviors will be compared between groups, as well as the level of emotional dysregulation, level of app engagement and time of psychiatric admission during the follow-up period.

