#### Secondary specific objectives

Analyze the frequency of self-injurious thoughts in the participants who receive the application with the frequency in those who do not receive the app.Establish that there is no increase in the frequency of self-injurious thoughts and behaviors in those participants who receive the application compared to the baseline levels at study onset.To explore whether the effectiveness of CALMA in reducing the frequency of self-injurious thoughts and behaviors is mediated by improved emotional regulation.Describe the levels of app engagement by the adolescent participants who used it during this study.To compare the time to psychiatric admission during the follow-up period in the participants enrolled who received the app with those participants who did not receive the app.

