##### Emotional dysregulation

Emotional dysregulation will be quantified with the validation in Spanish of the Emotional Regulation Difficulties Scale (DERS) (70). The original scale has 36 items with a Likert response format of 5 positions (from 1 = almost never, to 5 = almost always) and a structure of six factors: (1) Impulse control difficulties (6 items: “When I’m upset, I lose control over my behavior,” for example); (2) Limited access to emotion regulation strategies (8 items: “When I’m upset, I believe there is nothing I can do to make myself feel better,” for example); (3) Nonacceptance of emotional responses (6 items: “When I’m upset, I feel ashamed at myself for feeling that way,” for example); (4) Difficulty engaging in Goal-directed behavior (5 items: “When I’m upset, I have difficulty concentrating,” for example); (5) Lack of emotional awareness (6 reverse-scored items: “I am attentive to my feelings,” for example) and (6) Lack of emotional clarity (5 items: “I am confused about how I feel,” for example). The DERS has previously been used in pre-post intervention studies as a state variable of emotional dysregulation to assess effectiveness (71–74). This variable will be considered and analyzed as a quantitative variable.

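### Emotional dysregulation is to be compared between groups, but the only DERS test in the analysis section is the Sobel mediation test, so the app's effect on DERS would go untested

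*Protocol article*

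**What the plan says.** - **Abstract, Methods.** After naming the change in behaviour frequency, the sentence on outcomes continues: "will be compared between groups, as well as the level of emotional dysregulation, level of app engagement and time of psychiatric admission".
- **Secondary outcome measures, Emotional dysregulation.** DERS is listed here for this trial, with the statement "This variable will be considered and analyzed as a quantitative variable". Under Participant timeline it is given to both arms at baseline and at day 90, but not at day 30 or day 60.
- **Secondary specific objectives.** Emotional regulation appears once, as a mediator: "To explore whether the effectiveness of CALMA in reducing the frequency of self-injurious thoughts and behaviors is mediated by improved emotional regulation".
- **Statistical analysis, arm comparison.** The t-test, with Mann–Whitney as the alternative, is described for behaviours only: "the mean differences for each behavior between both groups will be compared using the t-Student test".
- **Statistical analysis, DERS.** The change from baseline is computed for the mediation step ("the difference between the value of the DERS scale at the last follow-up and the baseline will be calculated, and the Sobel test"). The regression for that step is one "whose dependent variable will be the difference in the frequency of each behavior and the independent variable will be the treatment". The only other mention of DERS in the section is in the imputation of missing values.

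**The concern.** The Sobel test concerns a product of two paths: app to DERS change, and DERS change to behaviour change. It can be non-significant because either path is weak. It therefore does not answer the simpler question that the abstract raises, which is whether DERS differs between the arms.

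Emotional regulation is the mechanism that the Intervention section proposes for the app, and the Discussion intends to draw a conclusion from it. If no arm comparison is fixed in advance, any DERS contrast reported later will have had its test, scale and adjustment chosen after the data were seen. If none is reported, a listed secondary outcome is left without a result.

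**Working it through.** **1. Where DERS is used.** Taking Statistical analysis in order, tests are named for sociodemographic variables (chi-square or Fisher, t or Mann–Whitney), for the change in each behaviour (t or Mann–Whitney, Bonferroni) and for mediation (Sobel). Multiple imputation follows. DERS occurs only in the last two. No sentence commits to testing or reporting DERS by arm.

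**2. Inputs.** From Sample size: 25 evaluable per group, two-sided 5% level, d = 0.85. The 25 is reproduced closely: a noncentral-t calculation with Mann–Whitney efficiency 3/π gives 24, and with the minimum efficiency of 0.864 gives 27. That d was set for behaviour frequency. The protocol gives no DERS effect and no slope linking DERS change to behaviour change, so both are assumed here over a range: effect a = 0.5 or 0.85 SD of DERS change, slope b = 0.2 to 0.7.

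**3. Direct test of DERS change.** Noncentrality is a·√(n/2), the critical t on 48 df is 2.011.
- a = 0.85: 0.85 × √12.5 = 3.01, power 84%.
- a = 0.5: 0.5 × √12.5 = 1.77, power 41%.

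**4. Sobel test.** z = ab / √(a²·SE_b² + b²·SE_a²). Equivalently, 1/z² = 1/z_a² + 1/z_b², where z_a = a/SE_a and z_b = b/SE_b. So the Sobel z is always smaller in size than z_a, which is in essence the direct test.

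With unit error variances, SE_a = √(2/25) = 0.283 and SE_b is about 1/√48 = 0.144. For a = 0.85 and b = 0.3, z_a = 3.01 and z_b = 2.08. Then 1/z² = 0.111 + 0.231 = 0.342 and z = 1.71, below 1.96.

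**5. Simulated power.** The Sobel statistic is not normal at this size, so power was simulated: 25 per arm, normal errors, no direct effect of the app on behaviour, unit error variance. Repeat runs agree to within about 1 or 2 percentage points.

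| Assumed DERS effect | Direct test | Sobel, b = 0.2 | b = 0.3 | b = 0.5 |
|---|---|---|---|---|
| 0.85 SD | 84% | 11% | 25% | 62% |
| 0.5 SD | 41% | 3% | 8% | 23% |

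**6. Sensitivity to scaling.** If the error variance of behaviour change is set to 1 − b² instead, Sobel power at 0.85 SD is 28% (b = 0.3), 70% (b = 0.5) and 83% (b = 0.7). At 0.5 SD it is 9%, 28% and 39%. At a slope of 0.7 on this scaling the two tests are nearly level (83% against 84%, and 39% against 41%).

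**7. The case b = 0.** At 0.85 SD the Sobel test rejects about 1.5% of the time. The indirect effect is then truly zero, so this is a false-positive rate and not power.

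**The case against.** **The plan matches its objective.** The only stated objective that involves emotional regulation is mediation, in exploratory wording, and the Sobel test addresses it. This stands. It does not cover the abstract's statement or the listing of DERS as a secondary outcome, both of which go further than that objective.

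**The abstract sentence is loose.** It also lists app engagement among the things compared between groups, although controls do not receive the app. So it cannot be read literally as a list of tests, and this weakens the point. But DERS, unlike engagement, is measured in both arms and can be compared.

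**A full analysis plan may add the test.** It may. If the article were merely silent, this would be no finding. Here two stated places disagree: one announces a comparison, and a fairly detailed analysis section gives DERS a different test.

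**The Sobel calculation already estimates the app-to-DERS path.** True: that path is the between-arm difference in DERS change. But the section does not commit to testing or reporting it.

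**Stronger readings that the documents do not support.** A reader might infer that a real effect on DERS would be reported as null. It would not follow: a non-significant Sobel test is a null on mediation, and the DERS effect would be untested. A reader might also take the phrase "as a state variable of emotional dysregulation to assess effectiveness" as this trial's own purpose for DERS. That sentence describes how earlier studies used the scale.

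**Conclusion.** The point holds as a mismatch between stated parts of the protocol. The abstract announces a DERS comparison and the outcome section lists DERS as a quantitative secondary outcome, but the analysis section supplies only a mediation test, which answers another question.

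The power figures show why the Sobel test is no substitute at weak to moderate slopes. They rest on assumed effects and slopes, on normal errors and on 25 evaluable per arm. The gap narrows as DERS change tracks behaviour change more closely and nearly closes at a slope of 0.7 under one scaling. The direct test is itself underpowered (41%) if the DERS effect is 0.5 SD, so the gain is a prespecified estimate of the effect and not an assurance of significance.

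The primary comparison is unaffected. The protocol should be changed here, because the change is small and the outcome is central to the app's rationale.

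**What to change.** Add to Statistical analysis a between-arm comparison of day-90 DERS in all randomised participants. Use linear regression on arm, adjusted for baseline DERS and hospital, with the planned multiple imputation, and report the adjusted difference with its 95% CI. The predictors now listed for imputation do not name arm; include it for this analysis, since leaving it out would pull the estimated difference towards zero. Keep the Sobel analysis as a separate step, labelled exploratory.

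Adjustment for baseline should also help precision. For an effect of 0.85 SD and an assumed baseline to day-90 correlation of 0.5, power rises from 84% to about 92%. At a correlation of 0.7 it is about 98% if the SD is that of the day-90 score, but about 89% if it is that of DERS change.

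The cost is one extra secondary analysis. It needs no new visits, data or participants.

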### Participant timeline

Clinicians will be asked to draw up a list of patients who have presented self-injurious behavior in the last month. With this list, the patients will be identified on the days that they attend the control by their psychiatrist or psychologist of each Service. After the usual control of the patient, one of the members of the research group will explain the purpose of the study to the participant and legal guardian. Next, the researcher will give them a copy of the consent and/or assent to read carefully and invite them to participate in the study. After the invitation, those who agree to participate will be scheduled for a 30-min interview with one of the research group members.

The first interview will be face-to-face and it will determine if the participant meets the inclusion criteria and sign the informed consent. Then, a series of clinical and demographic data will be requested and the Spanish version of the Self-Injurious Thoughts and Behaviors Interview (SITBI) and the Difficulties in Emotion Regulation Scale (DERS) will be administered. At the end of the interview, the follow up interviews will be scheduled and those patients randomized to the intervention group will have the application downloaded to their cell phones. In addition, they will be given a brief 5 to 10-min tutorial on how the app works, they will be given written material on its functioning, and they will be directed to the website where there will be explanatory material.^1^

Follow-up interviews (day-30 and day-60): those will be conducted *via* video call according to the epidemiological context of the COVID-19 pandemic. During these calls, only the SITBI will be administered and participants will be asked if they have had any hospitalization due to suicidal behavior in that period, and if so, the date of admission. In the intervention group, to guarantee engagement with the CALMA app, the rater will explore whether or not the participant has used the application. In case of not using it, the obstacles and the alternatives to overcome them will be determined through a brief protocol (DBT missing links strategy) to reinforce the use of the application during the next evaluation period. At the same time, the technical team will work throughout the study to guarantee the proper functioning of the app.

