The final interview (day-90) will be face-to-face or by video call depending on the epidemiological context of the COVID-19 pandemic. The SITBI, the DERS and, to those who received the app, the User Experience Questionnaire short version (UEQ-s) and a series of questions related to the opinion about the app will be administered. At the end of this interview, we will obtain data from the patient about the frequency of use of the app (subjective use report) and our information technology team will also obtain data on the use of the different functionalities of the app from each participant (objective use report). A flowchart describing how an individual participant will progress through the phases of the research process is outlined in Figure 6.

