In a prior pilot study, the CALMA app has shown initial evidence of safety and acceptability of the app for reducing self-injurious thoughts and behaviors when used as an adjunct to conventional DBT therapy within 4 weeks of follow-up (52). This study has shown good acceptability of CALMA as an adjunct to therapy targeting suicidal and non-suicidal self-injured behaviors. Furthermore, a high probability of decreased in SI, suicidal plan, suicidal gesture, thoughts about Non-Suicidal Self-Injury (NSSI) and NSSI pre-and post-intervention was observed in the group that received CALMA and a high probability of a greater decrease in SI and suicidal gesture before and after the intervention for the group that received CALMA compared to the comparison group.

This protocol describes a parallel-arm randomized controlled trial, which aims to test the efficacy, safety and acceptability of the CALMA application as an adjunct to therapy to reduce suicidal and non-suicidal self-injurious behaviors in adolescents.

This research will fill important gaps about the engagement and effectiveness of a DBT skills-based application in adolescents. Firstly, there are few studies of apps that focus on adolescents with suicidal behaviors, a population at higher risk of suicide and with distinctive characteristics (80); only some have the characteristic of being interactive with the user. Second, of the few studies that did measure effectiveness in this population, the results were negative. Third, this study is particularly relevant to young people given their widespread use of mobile technology, while there are currently no available mobile applications in Spanish at all that attempt to reduce suicidal behavior in this population (35, 81). Fourth, having a tool that can help reduce the probability of hospitalization for suicidal behavior that is economical, universal, and that is at the service of the crisis, such as an application, would undoubtedly democratize access to specific and effective intervention. Fifth, if the exploratory objective of this study demonstrates that the reduction of self-injurious behaviors is mediated by the improvement of emotional regulation, an app such as CALMA can be an invaluable tool to increase the capacity (skills) to manage intense and painful emotions.

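### The Sobel mediation test is conservative at this sample size, and with DERS taken only at days 0 and 90 it cannot show that emotion regulation changed before behaviour did

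*Protocol article*

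**What the plan says.** Mediation is a secondary objective of the Protocol article, worded as exploration: "To explore whether the effectiveness of CALMA in reducing the frequency of self-injurious thoughts and behaviors is mediated by improved emotional regulation". The Statistical analysis section defines the mediator: "the difference between the value of the DERS scale at the last follow-up and the baseline will be calculated". It then fixes the test: "the Sobel test will be used on a regression model whose dependent variable will be the difference in the frequency of each behavior", with treatment as the independent variable.

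The Participant timeline section sets when the data exist. SITBI and DERS are both given at the first interview. For days 30 and 60 it says "During these calls, only the SITBI will be administered". At day 90 the list is "The SITBI, the DERS and, to those who received the app", followed by the app questionnaires. DERS therefore has one post-baseline value.

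Behaviour change is calculated at every follow-up ("For all patients and at each follow-up moments, the difference between the frequency of each suicidal behavior and the baseline frequency will be calculated"), and the mediation text does not say which of these changes enters the model.

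The Discussion looks ahead to the result: "if the exploratory objective of this study demonstrates that the reduction of self-injurious behaviors is mediated by the improvement of emotional regulation", in which case the app is put forward as a means of building the capacity to manage intense emotions.

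**The concern.** **The test.** Sobel divides the product of two estimated coefficients by an approximate standard error and refers it to a normal distribution. In small samples that product is not close to normal, and the test rejects too rarely. A real indirect effect could be missed when a better interval would have found it at no extra cost.

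**The timing.** Mediation is a directional claim: the app improves regulation, and better regulation reduces self-injury. With regulation measured only at the two ends of follow-up, fewer self-injuries leading to a better DERS score fits the data as well as the reverse. A significant result could be read as evidence for the mechanism when the design cannot separate the two.

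**Working it through.** **1. The plan's own figure.** No power is stated for mediation. The Sample size section ("Considering a confidence level of 95%, a power of 80% and an effect size" of d = 0.85) covers only the two-sided Mann–Whitney comparison. A noncentral t calculation with n multiplied by 3/π (normal parent) gives 24 per group and 82.0% power at 25, so the stated 25 is reproduced within one patient. Mediation therefore has about 50 evaluable participants, or 58 if everyone randomised is counted.

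**2. Model and test.** The documents give neither the app's effect on DERS nor the link from DERS to behaviour, so both are assumptions here:
- M = a·X + e₁ and Y = b·M + e₂, where X is arm, M is DERS change and Y is behaviour change. Errors are standard normal, arms are equal and there is no direct effect.
- Sobel: z = âb̂ / √(b̂²·s²ₐ + â²·s²_b), significant if |z| > 1.96.
- Comparator: percentile bootstrap 95% interval for âb̂, significant if it excludes 0.

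**3. Rejection rates at n = 50** (simulated, rounded; repeated runs differ by one to three points):

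| a (SD) | slope b | Sobel | Bootstrap |
|---|---|---|---|
| 0.6 | 0.4 | 23% | 42% |
| 0.85 | 0.4 | 45% | 64% |
| 0.85 | 0.6 | 71% | 81% |
| 0 | 0.4 | 1.2% | 3.9% |

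The last row has no app effect on DERS, so its rates are false positives. Sobel falls well short of 5% and the bootstrap stays below it. At slope 0.8 the bootstrap rate is about 6%, so the gain in power is not bought with a materially inflated error rate.

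**4. A second parameterisation.** With b set as the within-arm correlation r of the two changes (20,000 replicates), Sobel power at n = 50 is 9% for a = 0.5, r = 0.3; 28% for 0.5, 0.5; 28% for 0.85, 0.3; 70% for 0.85, 0.5; and 82% for 0.85, 0.7. At n = 58 the last two are 80% and 88%. The scales agree: slope 0.6 with unit error SD means r = 0.6/√(1 + 0.36) = 0.51, and the two powers are 71% and 70%.

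**5. Temporal order.** This needs no assumption about effect sizes. DERS exists at days 0 and 90 only. If the outcome is behaviour change at day 90, the natural reading, both changes span the same interval. If it is the change at day 30 or 60, the outcome is measured before the mediator. In neither case can the data place DERS change first.

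**6. What a reversed mechanism would look like.** Let the app act on behaviour and behaviour act on DERS: Y = 0.85·X + e, M = 0.7·Y + e. DERS mediates nothing. The planned models would nevertheless estimate:
- app to DERS: 0.7 × 0.85 = 0.595
- DERS to behaviour given arm: 0.7/(0.7² + 1) = 0.47
- apparent indirect effect: 0.595 × 0.47 = 0.28

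At n = 50 Sobel is significant in about 32% of such trials and the bootstrap in about 41%. At slope 1.0 the figures are 53% and 58%. At slope 0.4 Sobel gives about 7%. A better test does not cure the direction problem.

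**The case against.** The strongest reply is that this is a secondary, openly exploratory analysis. Neither the primary comparison nor the sample size rests on it, low power is usual for mediation in a small trial, and the Discussion sentence is conditional. That stands, and it limits the weight of the point. It does not remove it, because the same sentence treats a positive result as capable of establishing mediation.

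Some stronger readings are tempting and are not supported:
- *Skewed counts make Sobel fail.* With lognormal outcome errors Sobel power was not lower: 55% against 68% for the bootstrap at (0.85, 0.4), and 29% against 46% at (0.6, 0.4). This was a continuous skewed error, not a count model, but it gives no support to skewness as the cause. The plan also provides for checking distributions and transforming. The conservatism comes from the product of coefficients.
- *The analysis is underpowered, full stop.* The path sizes are assumed. With a = 0.85 and r = 0.7, Sobel reaches 82% at n = 50. Because missing values are to be multiply imputed, the effective size may lie between 50 and 58.
- *Both changes are taken at the final visit.* This is explicit for DERS and only inferred for behaviour.
- *A day-60 DERS would settle direction.* It would improve ordering, but DERS is not randomised, so common causes of DERS and behaviour would remain. The Randomization section is in the past tense, so some participants may already be beyond day 60.

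A statistical analysis plan could change the test. It could not supply a DERS measurement that was never taken.

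**Conclusion.** The point holds in a limited form. That the planned data cannot show emotion regulation changing first follows from the visit schedule alone. That Sobel is an inferior choice at this size is also firm: in the scenarios compared with the bootstrap it lost about 10 to 20 percentage points of power, and its false-positive rate with no app effect on DERS was about 1% at slope 0.4. The absolute power, about 23% to 71% for Sobel and 42% to 81% for the bootstrap, depends on the assumed paths and on normal errors with n = 50. The bootstrap narrows the power gap without closing it. Nothing here bears on the validity of the primary comparison. The consequence is confined to the mediation result and what may be concluded from it.

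**What to change.** In Statistical analysis:
- Replace the Sobel test with a bootstrap 95% confidence interval for the indirect effect, and state how it is combined with the planned multiple imputation.
- Adjust both the mediator and the outcome model for baseline DERS, baseline frequency of the behaviour and hospital.
- Name behaviour change at day 90 as the outcome.

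In Statistical analysis and Discussion, state that the mediation result is exploratory and shows association, not direction or demonstrated mediation.

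Optionally, where still feasible, add DERS to the day-60 call and relate its change to day-90 behaviour, while acknowledging that confounding remains.

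The required changes cost slightly more analysis work and a more modest conclusion. The optional one adds a 36-item questionnaire to a call now confined to the SITBI, the admission questions and, in the app arm, the review of app use. It would be incomplete for anyone already past day 60.
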